### Statistical analysis

2.7

The “intention to treat” analysis method will be adopted in this study. A simple comparison for rates of SDH, mortality, and cerebral vasospasm will be made by *χ*^2^ test or Fisher exact test. The functional outcomes will be analyzed by Mann–Whitney *U* test. The log-rank method will be used with regard to the analysis of time-to-event type of outcomes. Preset subgroup (including age, location of aneurysm, WFNS grades, Fisher grade, time to randomization, time to operation) analysis will be performed. We will use logistic regression model to adjust the effect of multiple variables.

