#### Randomization

2.3.2

Patients will be allocated to either single aneurysm clipping group or aneurysm clipping plus FLT group by the minimization method that is performed by a minimization software. The stratification factors for minimization include age, Fisher grade, admission GCS, and acute hydrocephalus. Once a patient is qualified, the baseline information including demographics, medical history, time from SAH onset, Hunt–Hess grade, Fisher grade, and physical examination of the patient will be sent to a special researcher who is in charge of patients randomization.

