#### Primary outcome

2.6.1

The primary outcome of this trial is the incidence of shunt-dependent hydrocephalus confirmed by both clinical symptoms and CT scan at 1 year after operation. Clinical manifestation includes a progressive decline in neurological function (deterioration of mental status, urinary incontinence, gait disturbance, and memory impairment). The radiographic diagnosis of hydrocephalus is made on the basis of the ventriculomegaly with the following observations: enlarged frontal and temporal horns, enlargement of the third ventricle, a narrowed pattern of cortical sulci, and the presence of periventricular oozing. Ventricular size is determined by the cerebral ventricular index (the greatest width between the frontal horns at the level of the Monro foramen divided by the transverse inner distance of the cranium at the same level).^[26]^ Radiologically, hydrocephalus is diagnosed when the ventricular size exceeds the 95th percentile after adjusting for patient age. Whether or not shunt is placed depends on the following criteria: ventricular enlargement on radiological imaging stated above, the progressive neurological dysfunction, and the consequent improvement after lumbar drainage.^[31]^

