#### Sample size

2.6.3

The rate of SDH after anterior circulation aneurysm clipping was reported to range from 9.8% to 36% with an average rate of about 20% ,^[3,9,21]^ while the incidence of SDH was less than 5% in patients undergoing fenestration during aneurysm repair.^[8]^ We hypothesize that FLT can reduce the incidence of SDH from 20% to 5%. When statistical power is chosen to be 80% and a significant level to be 0.05 with a consideration of 10% loss to follow-up, a total of 288 patients are yielded with 144 patients in each arm.

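### Patients are minimized on four factors, but the only test named for the primary outcome ignores them: mildly conservative if the factors are prognostic, and cheap to fix

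*Protocol article*

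**What the plan says.** Section 2.3.2 (Randomization) allocates patients "by the minimization method that is performed by a minimization software". It names four factors: "The stratification factors for minimization include age, Fisher grade, admission GCS, and acute hydrocephalus".

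Section 2.6.1 makes SDH a binary outcome at one year: "The primary outcome of this trial is the incidence of shunt-dependent hydrocephalus confirmed by both clinical symptoms and CT scan at 1 year after operation".

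Section 2.7 (Statistical analysis) then says: "A simple comparison for rates of SDH, mortality, and cerebral vasospasm will be made by" chi-square or Fisher exact test. It closes with one further sentence: "We will use logistic regression model to adjust the effect of multiple variables". That sentence does not say which outcome is modelled, which covariates enter, or whether the model is the main or a supporting analysis.

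**The concern.** Minimization forces the arms to be alike on the chosen factors. If those factors predict SDH, the difference in SDH rates varies less from trial to trial than it would under simple randomization. A chi-square test uses the simple-randomization variance, which is then too large. The test rejects less often than its nominal 5%, some power is lost, and any interval built on the same variance is too wide.

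The Background gives reason to expect some prognostic value. It calls high-grade haemorrhage a risk factor for SDH and says that patients with low Hunt–Hess or Fisher grades develop it much less often. At stake is a modest loss of efficiency in a trial that expects only about 32 to 33 primary events.

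**Working it through.** **Inputs from the article.** SDH 20% in controls and 5% with fenestration; 80% power; significance level 0.05 (sidedness not stated, taken as two-sided); 10% loss; 288 patients, 144 per arm. Evaluable patients: 144 × 0.9 = 129.6, taken as 129 per arm, 258 in total. Expected events: 129 × (0.20 + 0.05) = 32.25.

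**The plan's own figure.** n per arm = [z₀.₉₇₅√(2p̄(1−p̄)) + z₀.₈₀√(p₁(1−p₁) + p₂(1−p₂))]² / (p₁−p₂)², with p̄ = 0.125.

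- [1.960 × √0.21875 + 0.842 × √0.2075]² / 0.15² = (0.917 + 0.383)² / 0.0225 ≈ 75.1, so 76 per arm.
- 76 / 0.9 = 84.4, so 85 per arm and 170 in total. With continuity correction: 88 per arm, 98 after loss, 196 in total.

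The stated 288 is therefore not reproduced at 80% power. That is a separate matter and this point does not depend on it. It does mean that 129 evaluable per arm carry about 96% power for 20% vs 5% by the same formula (95% for the exact Fisher test).

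**Mechanism.** Var(Y) = E[Var(Y|X)] + Var(E[Y|X]), where X are the minimization factors. Balancing X largely removes the second term from the sampling variance of the difference in rates. The chi-square test still counts it. If X is not prognostic, the second term is zero and nothing is lost.

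**Simulation.** Minimization with a biased coin of 0.8 on four binary factors, with prevalences 0.5, 0.5, 0.5 and 0.3 and the same odds ratio (OR) for each factor. All of these are assumptions: the article gives neither the random element nor any odds ratio. Overall event rates were held at the stated values. There were 5,000 runs under the null and 1,500 to 2,000 under each alternative. The adjusted test is a likelihood-ratio test in a logistic model with the four factors.

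| Quantity | Test | OR 1 | OR 1.5 | OR 2 | OR 3 |
|---|---|---|---|---|---|
| Type I error, N=258 | chi-square | 4.9% | 4.6% | 3.9% | 3.5% |
| | Fisher | 3.9% | 3.5% | 2.9% | 2.4% |
| | adjusted | 5.2% | 5.2% | 4.8% | 5.3% |
| Power, 20% vs 5%, N=258 | chi-square | 97.0% | 95.8% | 96.3% | 97.2% |
| | adjusted | 97.1% | 96.5% | 97.0% | 98.2% |
| Power, 20% vs 10%, N=258 | chi-square | 60.1% | 62.9% | 63.7% | 62.2% |
| | adjusted | 61.7% | 64.7% | 66.6% | 68.6% |
| Power, 20% vs 5%, N=152 | chi-square | 84.0% | 83.8% | 82.7% | 83.2% |
| | adjusted | 85.5% | 85.3% | 85.5% | 87.2% |

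Monte Carlo standard errors are about 0.3 points for type I error, 0.4 to 0.5 for power at 20% vs 5% with N=258, and about 1 for the other power rows.

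**Reading the table.**

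- At the design effect and N=258, adjustment gains 0.1 to 1.0 points.
- At 20% vs 10%, an effect assumed here and not in the plan, it gains about 2 to 6 points.
- At N=152, the size the stated inputs require before loss, it gains about 1.5 to 4 points.
- At OR 1 adjustment can add nothing, yet the adjusted test is still about 1.5 points ahead at 20% vs 10% and at N=152. That part comes from using a likelihood-ratio test.
- Fisher's 3.9% at OR 1 is discreteness alone.

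**A second simulation** (4,000 trials per scenario, 130 per arm, stronger assumed factors) agrees in direction. Chi-square type I error was 4.0% with odds ratios of 1.7 to 3 and 3.5% with odds ratios of 2 to 5, against 5.2% and 5.1% adjusted.

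**The case against.** An adjusted analysis is already in section 2.7, and the section labels no test as primary. A condensed article may leave covariates and model status to a fuller document that is not shown. This stands in part. A reader might infer that the plan designates an unadjusted primary analysis and treats the logistic model as an afterthought; the text says neither. What remains is that the only test attached to SDH by name ignores the factors used for allocation, and nothing in the article links the adjusted model to them.

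The size rests on assumed odds ratios. This stands. The article gives none, and does not say why the four factors were chosen. Eligibility also narrows them: Fisher 3–4, Hunt–Hess 3–4, age 40 to under 70. The honest range therefore starts at no effect. A moderate effect is still plausible for acute hydrocephalus. The Background gives permanent shunting in about 30% of patients drained for it, against about 20% overall. These figures come from different studies. If 20% to 40% of patients had it (assumed), the rate in the others would be (0.20 − 0.30 × 0.2)/0.8 = 17.5% to (0.20 − 0.30 × 0.4)/0.6 = 13.3%, an odds ratio of about 2.0 to 2.8.

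A reader might also infer that, with so few events, the lost power endangers the trial. At the design effect it does not: power is about 96% to 97% with chi-square. The loss counts only if the true benefit is smaller. The Background makes that possible, since it cites a systematic review with 10% vs 14% and a small randomized trial with 24% vs 16%, the latter against fenestration.

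Finally, the unadjusted test remains valid, and its error is on the safe side. This stands in full.

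**Conclusion.** The point holds as a modest improvement in efficiency. The allocation method and the only test named for SDH do not match, and the adjusted model that could bring them together is left unattached.

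If the factors are prognostic, with an assumed odds ratio of up to 3 each, chi-square operates at about 3.5% to 4.6% instead of 5%, and Fisher at 2.4% to 3.5%. If they are not prognostic, chi-square loses nothing. The power given up by chi-square is about 1 point or less at 20% vs 5% with 258 evaluable patients, and about 2 to 6 points at 20% vs 10%, of which about 1.5 come from the choice of test.

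A reader might go on to infer that ignoring the minimization factors makes a positive result unreliable. It does not: false positives are not inflated, and a false claim of benefit does not become more likely. The figures depend on the assumed odds ratios, factor prevalences and biased coin. The effect on intervals follows from the same variance argument and was not simulated.

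**What to change.** In section 2.7, make the logistic regression already planned the primary analysis of SDH, with treatment and the four minimization factors as covariates. Use a likelihood-ratio or Firth-type test, because only about 33 events are expected. Report a marginal (standardized) risk difference with its 95% CI. Keep the chi-square or Fisher test as supportive.

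The cost is a few words and a few lines of code. No new data are needed, since the factors must be known at allocation. The one caution is sparse events: about 32.25 / 5 ≈ 6.5 per parameter, counting treatment and four covariates, which is why a likelihood-ratio or Firth-type test is advised. The simulation covered binary factors and the likelihood-ratio test; the Firth version and the standardized risk difference were not simulated.

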#### Blinding

2.3.3

In this trial, because both the patients and doctors cannot be blinded, the assessor must be blinded to guarantee the research quality. Other measures are further adopted. First, the outcomes will be evaluated by 2 independent investigators who participate in neither the allocation nor the treatment and the final results will be filled in electronic case reports forms (CRF) without any modification once they are confirmed. Second, patients and related medical staff will be instructed not to leak any information regarding the treatment before and during the outcome evaluation. In addition, a statistician who will perform the statistical analysis is not allowed to take part in the implementation of the clinical trial (Fig. 2).

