#### Exclusion criteria

2.4.2

1.SAH secondary to nonaneurysmal entities such as hemorrhagic diatheses, trauma, tumor, or arteriovenous malformation, cavernous malformation;2.Early death due to rebleeding or other complications before surgery;3.Patients of extreme clinical severity, such as those with no spontaneous breathing, bilateral dilated pupils, or Hunt–Hess grade 5;4.Prior hydrocephalus or ventriculoperitoneal shunt, endoscopic third ventriculostomy, or FLT;5.Aneurysm beyond the access of surgical FLT including the distal anterior/middle cerebral aneurysms;6.DSA-negative SAH;7.Coagulopathy, or other known definite contraindication to operation;8.Patients complicated with vital organ dysfunction;9.Patient with poor compliance;10.Pregnant;11.Prior dementia or modified Rankin score (mRS) ≥3.

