### Intervention

2.5

Patients allocated in the control group will undergo standard microsurgical aneurysm clipping via pterion approach within 3 days after stroke onset. Sharp dissection of sylvian cistern, and then carotid, chiasmatic cisterns will be made to decrease intracranial pressure and expose the aneurysm according to the preoperative angiography. The Liliequist membrane will also be opened. The neck of aneurysm is seen clearly and clipped correctly avoiding the near perforating artery occlusion and parental artery narrowing under microscope of high resolution. The subarachnoid clot around the basal cistern will be meticulously cleared away. We do not routinely perform ventriculostomy that is reserved for patients with decreased consciousness and acute hydrocephalus.

Patients in the interventional group will undergo an additional fenestration of laminal terminalis after the same aneurysm clipping procedure. FLT will be performed in the following steps: a self-retaining retractor adjusted parallel to the anterior communicating artery to completely expose the lamina terminalis that is a bluish, bulging membrane behind the optic chiasm; an incision about 5 mm in length made strictly in the midline of the lamina terminalis to avoid injury to the adjacent neurovascular structures; the opened rim briefly coagulated to avoid subsequent reclosure as a result of adhesions. Postoperatively, standard medical treatment will be used in accordance with the recommendation of the professional guideline.

The trial will be terminated in advance if apparent benefit or higher rate of severe AE in one of the 2 interventions is revealed at a high significance level that is defined as differences of more than 3 standard deviations. To improve the adherence of protocol intervention, surgeons are not allowed to change the interventional strategy once the randomized grouping is determined. In addition, the video record of the entire surgical process will be checked at random to monitor the consistency of intervention. External CSF drainage is prohibited during the operation in the trial.

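### The preset subgroup by time to operation is completed only after allocation in an open-label trial, so randomization does not guarantee comparable arms within its strata

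*Protocol article*

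**What the plan says.** The commitment is in section 2.7 (Statistical analysis): "Preset subgroup (including age, location of aneurysm, WFNS grades, Fisher grade, time to randomization, time to operation) analysis will be performed". The list ends with two separate timing items, "time to randomization, time to operation", and the second is the one at issue. The same section declares an intention-to-treat analysis. It does not say where the clock for time to operation starts, and it attaches no caution to that item.

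Four other places fix the order of events and who knows the allocation:

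- Section 2.3.2 (Randomization) places allocation at qualification, on baseline data: "Once a patient is qualified, the baseline information including demographics, medical history, time from SAH onset". The minimization factors are age, Fisher grade, admission GCS and acute hydrocephalus. None is a timing variable.
- Section 2.5 (Intervention) describes the operation as what allocated patients then receive: "Patients allocated in the control group will undergo standard microsurgical aneurysm clipping via pterion approach within 3 days after stroke onset". The FLT arm has the same clipping plus the fenestration. On conduct after allocation the section says "surgeons are not allowed to change the interventional strategy once the randomized grouping is determined", which covers the type of operation and not its timing.
- Section 2.3.3 (Blinding) states that "because both the patients and doctors cannot be blinded".
- Section 2.4.2 (Exclusion criteria) lists "Early death due to rebleeding or other complications before surgery".

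**The concern.** A subgroup comparison keeps the protection of randomization only if the subgroup is defined by something that allocation cannot influence. On an ordinary reading, age, aneurysm location, the admission grades and time to randomization all meet that test. Time to operation does not, because its end point always falls after allocation.

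If the arm affects how soon patients are operated on, or which patients go early, the early stratum holds a different mix of patients in each arm, and so does the late one. SDH rates can then differ by arm within strata, in opposite directions, when FLT does nothing for anyone. The word preset would lend such a finding credibility, and an effect that seems to depend on early or late surgery is one that surgeons could act on.

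A second, smaller difficulty is that an allocated patient who never reaches surgery has no operation time and cannot be placed in either stratum.

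**Working it through.** **Step 1: order of events.** The sequence is qualification, allocation (2.3.2), then the allocated operation (2.5). Whether the clock starts at ictus, admission or randomization, it stops at surgery, after allocation. If it starts at ictus, part of the interval precedes allocation, but the full value does not. Time to randomization stops at allocation and is safe.

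**Step 2: what is needed for bias.** A post-allocation variable does not bias a subgroup comparison by itself. Timing, or its link with prognosis, must differ between arms. The protocol gives no figure on this and has no figure of its own to reproduce, so the rest is illustration with assumed inputs.

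**Step 3: mixture arithmetic, no FLT effect.** Assume half the patients are high risk (SDH 30%) and half low risk (10%), so that overall SDH is 20%, the control rate in section 2.6.3. Let eH and eL be the proportions of high-risk and low-risk patients operated on early.

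- SDH among early = (0.5·eH·0.30 + 0.5·eL·0.10) / (0.5·eH + 0.5·eL)
- SDH among late = the same, with 1 − e in place of e

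| Arm and assumption | eH, eL | Early SDH | Late SDH |
|---|---|---|---|
| Control | 0.6, 0.6 | 20.0% | 20.0% |
| FLT, case A | 0.5, 0.7 | (0.075 + 0.035)/0.6 = 18.3% | (0.075 + 0.015)/0.4 = 22.5% |
| FLT, case B | 0.4, 0.8 | (0.06 + 0.04)/0.6 = 16.7% | (0.09 + 0.01)/0.4 = 25.0% |

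False interaction (late difference minus early difference):

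- Case A: (22.5 − 20) − (18.3 − 20) = 4.2 points
- Case B: (25 − 20) − (16.7 − 20) = 8.3 points

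The overall FLT rate stays at 20% in both cases (0.6 × 18.3 + 0.4 × 22.5 = 20; 0.6 × 16.7 + 0.4 × 25 = 20), so the primary comparison is untouched.

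**Step 4: against sampling error.** Section 2.6.3 gives 144 per arm and 10% loss: 144 × 0.9 ≈ 130 analysed per arm, or 78 early and 52 late at 60/40. The variance of the interaction contrast is the sum of p(1 − p)/n over the four cells.

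- Case A: 0.0019 + 0.0021 + 0.0034 + 0.0031 ≈ 0.0104; SE ≈ 10.2 points; 4.2/10.2 ≈ 0.4 SE
- Case B: 0.0018 + 0.0021 + 0.0036 + 0.0031 ≈ 0.0105; SE ≈ 10.3 points; 8.3/10.3 ≈ 0.8 SE

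Rejection by a two-sided 5% test is Φ(z − 1.96) + Φ(−z − 1.96): about 7% in case A and 13% in case B.

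**Step 5: a second model.** Let a latent severity raise the log-odds of SDH by 1 per SD and, in controls, the log-odds of early surgery by 1 per SD. Control SDH is about 19% and FLT has no effect. Cell rates come from 2 million simulated patients. Rejection is then computed for a two-sided 5% Wald test of interaction with 288 patients.

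| Dependence of timing on severity in FLT arm | OR early | OR late | Rejection |
|---|---|---|---|
| Same as control | 1.01 | 1.00 | 5% |
| Half as strong | 0.88 | 1.20 | 8% |
| None | 0.72 | 1.51 | 23% |
| Fully reversed | 0.48 | 2.08 | 66% |

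The first row shows that timing which follows severity equally in both arms does no harm. A split on a variable fixed before allocation behaves in the same way.

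**The case against.** The strongest case on the other side is that the documents give little reason to expect timing to differ by arm. FLT is one short added step, an incision of about 5 mm, after identical clipping. Admission must be within 72 hours of ictus, and clipping takes place within 3 days of onset; that window is written for controls, but the FLT arm has the same clipping. This stands, and it is why the likely bias is small. The larger rejection rates in Step 5 need the link between timing and severity to vanish or reverse in one arm, which no section suggests.

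A reader might infer more than the text supports in three ways:

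- **That surgeons who know the arm choose the operating time, or that the FLT operation is scheduled later because it is longer.** The article does not say who sets the time, when the allocation reaches the surgeon, or that FLT affects scheduling.
- **That the false interactions should be judged against the planned 15-point reduction (20% to 5%).** That is the main effect, which this subgroup does not touch. The relevant yardstick is the standard error of the interaction.
- **That deaths before surgery break intention to treat through this subgroup.** Section 2.4.2 already makes such deaths an exclusion from the whole trial. Any conflict with intention to treat belongs there and would not be cured by deleting a subgroup. What remains here is only that an allocated patient who does not reach surgery, for instance by withdrawing, has no value.

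It can also be said that cut-points, interaction tests and interpretation are commonly left to the analysis plan. That is so, and their absence is not criticised. The choice of variable, however, is stated in the protocol.

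**Conclusion.** The point holds as a minor one. Time to operation is completed after allocation in a trial where doctors and patients know the arm, so randomization does not guarantee comparable arms within its strata. It would go too far to say that the comparison is biased: what is lost is the guarantee, and bias follows only if timing, or who is operated on early, depends on arm.

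The order of events is certain from the text. The existence and size of any bias are not. With assumed moderate dependence on arm, the false interaction is 4.2 to 8.3 points, or 0.4 to 0.8 standard errors, and the false-positive rate rises from 5% to about 7% to 13%. More extreme assumptions raise it further, without support in the documents. One of six listed subgroups is affected; the primary analysis and the sample size are not.

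**What to change.** In section 2.7, remove time to operation from the preset effect-modifier subgroups and keep time to randomization, which is already listed and is fixed before allocation. Tabulate time to operation by arm as a description of treatment delivered, with the number of allocated patients who were not operated on. If any analysis by time to operation is reported, label it exploratory and non-randomized.

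The cost is one item deleted from a list and one descriptive table row. No extra data, patients or staff are needed, and no clinical rule changes.
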